# The More and Less Study: a randomized controlled trial testing different approaches to treat obesity in preschoolers

**DOI:** 10.1186/s12889-015-1912-1

**Published:** 2015-08-01

**Keywords:** Children, Eating behaviors, Feeding practices, Lifestyle, Obesity, Parenting, Preschoolers, Self-efficacy, Socioeconomic status, Treatment

## Abstract

**Background:**

While obesity has been shown to be difficult to treat in school aged children and in adolescence, promising results have been detected for children who started treatment in early childhood. Yet knowledge on the effectiveness of structured early childhood obesity treatment programs is limited, preventing the widespread implementation of such programs. The main objective of this study is to evaluate the effectiveness of early treatment of childhood obesity with respect to treatment focus (parenting practices or lifestyle), length and intensity. The study will also examine the influence of gender, age, parental weight status, parenting practices, child behavior as well as parents’ socioeconomic status and child and parental psychosocial health on children’s weight status.

**Methods/design:**

This is a parallel open label randomized controlled trial assessing two different behavioral treatment approaches offered in three conditions to families with children aged 4–6 years in Stockholm County, Sweden. Children (n = 180) identified as obese will be referred from primary child health care, school health care, and from outpatient pediatric clinics, and randomized to: 1) a standard treatment with focus on lifestyle, provided within the current healthcare system (n = 90); 2) a 10-session, 1.5 h/week group treatment with focus on parenting (n = 45); or 3) the same group treatment as 2) with additional follow-up sessions (n = 45). The primary study outcome is change in children’s body mass index standard deviation score (BMI SDS) one year post-baseline. Secondary outcomes include changes in children’s waist circumference, metabolic health, lifestyle patterns (Food Frequency Questionnaire), obesity-related child behaviors (Child Eating Behavior Questionnaire and Lifestyle Behavior Checklist, Problem Scale), parents’ general and feeding parenting practices (Communicating with Children and Child Feeding Questionnaire) and lifestyle-specific self-efficacy (Lifestyle Behavior Checklist, Confidence Scale), family functioning (Family Assessment Device), child and parental psychosocial health (Child Behavior Checklist and Beck’s Depression Inventory II).

**Discussion:**

This study will facilitate a close examination of key components of treatment for obesity during early childhood and mechanisms of change. Results from this study will lead to better healthcare options for obesity treatment during early childhood and ultimately to the prevention of obesity later in life.

**Trial registration:**

ClinicalTrials.gov NCT01792531 Registered February 14, 2013.

## Introduction

While obesity has been shown to be difficult to treat in adults, adolescents and school-aged children, promising results have been seen for preschoolers. Yet knowledge on the effectiveness of structured childhood treatment programs for obesity early in life is still very limited, preventing the widespread implementation of such programs. The purpose of this paper is to present a study protocol for the randomized controlled trial, the More and Less Study (ML). The overarching aim of ML is to evaluate the effectiveness of early treatment of childhood obesity by evaluating two different treatment approaches offered in three conditions to families with children aged 4–6 years (n = 180) with obesity. The study is organized and performed within the healthcare system in Stockholm County, Sweden and participants are followed one year post-baseline.

## Background

### Early treatment

Although unprecedented high levels of obesity in children have been observed and discussed for more than a decade [1, 2], the effectiveness of managing childhood obesity in health care settings is not well-known. Reports from quality measurement organizations such as the Swedish Council on Technology Assessment in Health Care [3] and the Cochrane Collaboration [4, 5] conclude that the evidence for effective interventions in early childhood (≤5 years) is particularly limited. However, results from cohort studies indicate that early treatment can be more successful than treatment later in childhood. The first evidence for the efficacy of early childhood intervention was found in a study reporting long-term results from a cohort of over 600 children treated for obesity in Germany [6]. In this study, children in the youngest age group (4–7 years) clearly demonstrated the highest sustained decreases in body mass index standard deviation score (BMI SDS) at 5 years follow up after completing lifestyle treatment in comparison with children in older groups (8–10, 11–12 and 13–16 years) [7]. The findings were confirmed by researchers from the Karolinska Institutet (KI), demonstrating that if children with obesity were treated at younger ages (6–9 vs. 10–13 and 14–16 years) the results were significantly better 3 years after the treatment was initiated [8].

#### Length and intensity of treatment

There is no scientific agreement about the appropriate length or intensity of treatment in pediatric obesity. While obesity treatment in health care settings is usually low-intensive and spans many years, many classical structured obesity programs developed for children and adolescents are time-limited, usually lasting 3–4 months [4, 7, 9–12]. Brief interventions that build on a family’s existing resources can be equally effective in triggering successful and sustainable lifestyle modifications in comparison to more intensive efforts [9, 13, 14]. Braet and colleagues suggest that for a majority of children and adolescents a basic treatment proved to be enough [15]. Alternatively, others claim that continuous care is necessary due to the chronic nature of obesity [8, 16, 17]; thus, it would be unethical not to offer long-term treatment [18].

### Importance of parenting

The success of early interventions might be explained by allocating more attention to the role of parents in creating a healthy lifestyle for younger children [19, 20]. Parents ask for tools to manage their children’s problematic behavior (e.g., food fussiness especially with regard to vegetables, lack of satiety, emotional overeating and excessive screen time) [21]. Research indicates that parents of obese children report a higher frequency of these behaviors than parents with normal weight children [22] and also rate their confidence as lower in handling the problematic behaviors [23, 24].

Exclusive focus on parents in treatment has proved to be effective in improving child weight status [19, 20, 25–30]. Indirect focus on children might protect the child’s self-esteem [31], a concern commonly shared by parents [32]. Additionally, a parental focus has also shown to be a more cost-efficient and feasible approach [29, 33, 34]. Theoretically, programs targeting parents provide specific tools to parents over and above the standard recommendations around food and physical activity [35–38]. Tools can enhance general parenting and/or parenting practices in specific situations. General parenting is usually described as attitudes and beliefs that create an emotional climate and determine the behavioral expression between the child and the parent [39]. The four parenting styles commonly proposed in this context are: authoritative, authoritarian, permissive and neglectful [40, 41]. The parenting styles are built upon two dimensions of parental behavior; how responsive parents are to the child’s needs and how controlling they are of child behavior [40, 41]. An authoritative parenting style, characterized by being responsive to the child’s needs but able to set clear limits [40–42], has been associated with children eating healthier, having a higher physical activity level and a lower body mass index (BMI) [36, 43]. On the other hand, authoritarian, permissive and neglectful parenting styles have been associated to less healthy behaviors [36, 44]. However, the associations are affected by parenting practices in specific situations, such as feeding, as well as child and parental characteristics [36, 37, 39, 45–48]. Many researchers in childhood obesity have examined parental feeding practices, most often restriction [46, 49]. Restrictive and controlling feeding practices have been associated with a higher BMI in the child in many cross sectional studies [37, 50]. The relationships are less clear in longitudinal research [51, 52]. A better conceptualization of restriction and control is needed to understand the positive and negative effects on weight development [37, 45, 53, 54]. Parental monitoring has also been associated with healthy child behaviors and weight status, but the strength of associations is not as strong [49, 55–57], possibly due to parents awareness of the importance of such practices (social desirability) leading to high floor and ceiling effects in responses to items [58].

### General parenting as a treatment approach for preschool obesity

The predictive relationship between parents’ feeding practices and general parenting styles suggests a role for general parenting in childhood obesity interventions [59]. Parenting programs addressing general parenting aim to target child behavior indirectly by improving parents' knowledge, confidence and practices [60, 61]. Parents are made aware of specific behaviors that are effective when interacting with the child: encouragement, positive involvement, problem solving, emotional regulation, monitoring and limit setting strategies. These parenting practices have been linked to healthy child development and with a supportive family climate. On the other hand, behaviors such as inconsistent and over-reactive parenting practices have been shown to be maladaptive and are discouraged [60–63]. Few studies have included general parenting practices as part of a childhood obesity intervention [26, 28, 30, 64–66]; and only three studies have carefully assessed the changes in parenting practices during treatment [26, 28, 66] to establish the most important skills in shaping healthy lifestyles [35]. Moens and Braet conducted a pilot study targeting parents of school-aged children; the children’s weight status had improved 6 months post baseline; however, no changes were seen in general parenting practices which could be due to the small sample size [28]. In Australia, West and colleagues demonstrated promising results after a parenting program for parents with school-aged children; children’s weight status improved and parents increased their confidence in managing child obesity-related behaviors and used inconsistent or forceful parenting practices less frequently [26]. The same program was evaluated in the Netherlands but showed no long-term effects after twelve months [66]. Given the limitations of previous studies focusing on general parenting practices as a treatment approach for obesity and the lack of data for preschool aged children, there is a need for a new parenting focused program.

### Conceptual influences

Bandura’s Social Learning Theory [67] and Patterson’s Social Interaction Learning Theory [68, 69] state that children’s optimal development is promoted by active family involvement. Family members’ behavior modeling and effective interaction are therefore essential and result in a coherent and mutual understanding about responsibilities and role sharing. Equally important is the Ecological System Theory, developed by Bronfenbrenner [70], which further explains how children’s development is affected on many levels, not only by the microlevel contexts of their immediate environments (family, school, etc.). Child development is also influenced by mesolevel processes through which the children’s family, school, and other micro-environments interact, along with exolevel (community) and macrolevel (culture) contexts that do not involve the children directly [70]. Indeed, the cascading effects of Social Learning Theory based parenting programs, such as lower parental depression and improved families environment [71–73], demonstrate the direct and indirect contexts of child development.

#### Program development

One of the most effective parenting programs is KEEP (Keeping Foster and Kin Parents Supported and Trained). A major principle of KEEP, which is centered on Patterson’s Social Interaction Learning Theory, is that parents can serve as key agents of change for children. This is accomplished by strengthening caregiver confidence and skills so they can change their child’s behaviors, teaching effective parent management strategies, and providing them with support. Five dimensions of positive parenting form the cornerstone of KEEP. *Encouragement* involves the use of scaffolding (i.e., breaking complex behaviors into achievable steps and encouraging approximations toward the goal) and positive reinforcement to teach new behaviors. *Limit setting* involves using clear instructions and being consequent to discourage negative behaviors. *Monitoring* involves parental tracking of child whereabouts, activities, and behaviors and the provision of appropriate adult supervision. *Problem solving* involves setting goals, developing strategies to achieve goals, committing to the decision, trying it out, and making relevant adjustments. *Positive involvement* involves how parents show love and interest to their child [60, 74]. The intervention moves in a step-by-step fashion, with parents learning one positive parenting skill before adding new skills to their parenting tool box [60, 74]. Role play is used extensively as a teaching tool to help parents to understand situations from differing perspectives. Role play also provides practice with a group leader to ensure the use of skills from the group sessions to the home.

KEEP was developed by [name] and colleagues at the Oregon Social Learning Center (OSLC), a family research institute in the USA. As the intervention has been used previously with foster families in Sweden, a natural step was to use KEEP as a foundation for a childhood obesity parent program in Sweden. Modifications of the program are described under “Methods”.

According to our conceptual model (see Fig. 1), changes in general parenting (e.g., encouragement, limit setting) will modify specific parenting practices (e.g., meal and screen time situations and routines) that will consequently influence the child’s home environment and result in improved child obesity outcomes such as BMI SDS. An important supporting component in the new program is the *regulation of emotional expression* within each of the five positive parenting practices inspired by the Parent Management Training Oregon Model (PMTO) [71, 75].

**Fig. 1 Fig1:**
[figure not shown]
Conceptual model of the relationships between parenting and child weight status

### Mechanisms for treatment effect

Because parental behavior is affected by child characteristics and behaviors [39, 76, 77] the pathways for how these associations predict, mediate or moderate treatment results need to be assessed. Research on which dimensions of general child behaviors (internalizing and externalizing) that children with obesity are most vulnerable to is still inconclusive [78]. Identifying a child behavior profile before treatment start was proposed in a Dutch study as a way to direct families to a more appropriate obesity treatment [78]. In the same study the authors stressed that the weight status alone was not an indicator for psychological health [78]. Children’s eating behavior (based on research on appetitive traits) is also a behavioral risk factor for obesity that we will examine [79]. Children with overweight and obesity tend to be more responsive to food and enjoy food more, have a higher degree of emotional eating, lower response to internal satiety cues and are less fussy when it comes to food compared to healthy weight peers [80].

Among moderators, parental depression may have especially profound consequences on treatment outcomes. Parental depression has previously shown moderating effects on parenting style as well as for specific practices and child obesity; depressed mothers were more permissive and used less controlling feeding practices [52, 81].

Family’s socioeconomic status (SES) measured as parental education is usually assessed in interventions and has been linked to treatment outcomes [82–85]. Other components of SES such as income, social support (functional and structural), family and household structure and economic stress have not yet been examined in detail; such examinations would lead to a better understanding of the influence of other factors beyond education. Parent’s foreign origin is another background factor of influence for a healthy lifestyle such as children’s dietary intake [86, 87].

### Aims and hypothesis

The overarching aim of ML is to evaluate two different treatment approaches for obesity in preschool aged children offered in three conditions. The specific aims are:To determine the effectiveness of two obesity treatment approaches: 1) standard treatment (n = 90) and 2) parent group treatment (with and without booster sessions) (n = 90). The two approaches will be evaluated with respect to child weight status, BMI SDS (primary outcome). The secondary outcomes for the child will be: lifestyle patterns, child eating and obesity related behavior, metabolic and psychosocial health; for parents: family functioning, parental feeding and limit setting practices, confidence and depression.To examine the influence of treatment length and intensity (as defined by group attendance and participation in booster sessions) for the two different parent group conditions; 1) 10 weekly 1.5 h sessions (n = 45) and 2) 10 weekly 1.5 h sessions plus booster sessions every 6 weeks during the remaining time of the study (n = 45).To examine predictors, moderators and mediators of treatment effects. We will assess whether changes in general practices (limit setting and emotional regulation) and parental feeding practices (restriction, pressure to eat and monitoring) will mediate child obesity outcomes by examining all treatment groups. In addition, we will examine predictors and moderators of intervention effects (e.g., age, gender, socioeconomic status (SES), child eating behavior, child psychosocial health, parental confidence, weight status, and depression).

We hypothesize that the ML parent group treatment, which addresses obesity in preschool aged children, will be effective in improving both primary and secondary outcomes. We expect that core elements of the parent group program (i.e., encouragement, positive involvement, problem solving, emotional regulation, monitoring, and limit setting strategies) will have additional beneficial effects on child weight status by helping parents to support health-promoting routines and habits around food/beverage consumption and physical activity practices to reduce sedentary behaviors compared to standard treatment; see our conceptual model in Fig. 1. Further, we assume that additional booster sessions in the parent group treatment condition will significantly improve treatment outcomes showing that regular follow-up is necessary in the treatment of childhood obesity.

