## Methods/Design

### Design of the study

This is a parallel open label randomized controlled trial comparing effects of two obesity treatment approaches for 4–6 year old children: standard treatment as offered in pediatric clinics in Stockholm County, Sweden, and a parent group treatment focusing on parenting practices supporting healthy lifestyle changes. The parent group treatment is offered in two conditions in order to assess the effects of treatment intensity and length. The trial commenced 2011 and will run until 2017.

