#### Allocation

Eligible families are randomly assigned (2:1:1) to one of three treatment conditions (standard treatment, parent group treatment with booster sessions, parent group treatment without booster sessions) using an electronic randomization program with permuted blocks. Randomization sequence is maintained by the study statistician to assure concealment. Neither the parent group leaders nor the families are informed about which families are allocated to boosters until after the groups are finished in order to avoid differential treatment (Fig. 2).

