The initial training of the ML group leaders was conducted by the KEEP developers. The five-day experiential training included information on the program’s theory and practice in the delivery of group sessions. During the training each session of the ML program was thoroughly discussed and each trainee role practiced facilitating several key sessions while other trainees acted as parents. The training then continued through external supervision from the KEEP developer group; all parent group sessions were videotaped using a laptop with software that enables the recording to be uploaded to a secure website and were translated to English. The KEEP consultant viewed the recordings, rated them for fidelity, and identified areas for reinforcement and feedback. The recordings then were used in weekly consultation meetings (1 h each). Prior to the consultation, group leaders completed a session review form with questions about what went well and challenges experienced. They also completed weekly forms on parent attendance and engagement ratings. Each of these measures informed the consultation process. After completing three supervised groups the group leader can apply for certification as ML leader. After certification by the KEEP model developers, the group leaders receive bi-annual fidelity checks. After co-leading two groups, a co-leader person can apply for certification after additional supervision during one group as group leader.

Families allocated to booster sessions receive phone calls every four to six weeks for the remaining nine months of the study. During these 30 min calls, parents are encouraged to maintain lifestyle changes regarding food and physical activity/sedentary behaviors already made, as well as receive support for new challenges they are facing. Subsequent calls begin with a follow-up of what was discussed during the previous call. In the booster sessions the parents are also referred back to discussions held during the program and to the manual for additional support.

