### Primary and secondary outcomes

The outcome measures are collected at baseline, 3-, 6- and 12-months post-baseline; see primary and secondary outcome measures in Table 2. The primary outcome measure is BMI SDS, derived from Swedish age and gender specific reference values [97]. Body mass index (BMI) (= weight in kilograms/height in meter^2^) will be calculated to be able to create weight status categories according to international cut-offs [93] to be able to examine changes during the study time.

**Table 2 Tab2:** Socio-demographic characteristics and outcome measures collected at different time points

		Measure	Baseline	3 months	6 months	12 months

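### Aim 2 mixes the randomised booster comparison with attendance and booster participation, which arise after randomisation

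*Protocol article*

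**What the plan says.** Under Aims and hypothesis, Aim 2 sets out to examine treatment length and intensity, "as defined by group attendance and participation in booster sessions". The same sentence applies this "for the two different parent group conditions; 1) 10 weekly 1.5 h sessions (n = 45") and names a second condition of 45 families who also receive boosters.

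Elsewhere the question is framed by condition. The hypothesis is that "additional booster sessions in the parent group treatment condition will significantly improve treatment outcomes", from which the authors expect to show that continued follow-up is needed. Design of the study says: "The parent group treatment is offered in two conditions in order to assess the effects of treatment intensity and length". Allocation says: "Eligible families are randomly assigned (2:1:1) to one of three treatment conditions", and adds: "Neither the parent group leaders nor the families are informed about which families are allocated to boosters until after the groups are finished".

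On timing, the section on parent group treatment says: "Families allocated to booster sessions receive phone calls every four to six weeks for the remaining nine months of the study". Primary and secondary outcomes says: "The outcome measures are collected at baseline, 3-, 6- and 12-months post-baseline".

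The Statistical analysis section gives example models labelled for Aims 1 and 3, and none for Aim 2.

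**The concern.** How many sessions a family attends, and how many booster calls it takes, is decided after randomisation and partly by the family. Motivation, stress, socioeconomic status and early success may affect both that decision and the child's BMI SDS. A contrast built on what families took up therefore loses the protection of randomisation. Engaged families could look better whether or not boosters work.

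The intended conclusion is causal: continued follow-up is needed, and the Conclusions section promises to identify the optimal length and intensity. Only the contrast by allocation can carry such a claim. An analysis plan written from Aim 2 as it stands could follow either definition, and the two may disagree.

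**Working it through.** **1. The two definitions side by side.** The named conditions are randomised arms. The definition attached to them is group attendance plus booster participation.
- *Booster participation* overlaps with allocation, since only families allocated to boosters are called. It is not the same thing, because an allocated family may take few calls or none.
- *Group attendance* refers to the ten sessions that both parent-group arms receive alike, with booster allocation not disclosed to leaders or families until the groups end. It was never randomised and cannot stand for allocation. An intensity measure built on it can only be observational.

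**2. Are confounders plausible?** The article supplies candidates. It links socioeconomic status to treatment outcome (Mechanisms for treatment effect). It expects higher 12-month BMI SDS where parents are more depressed (Statistical analysis). It ties motivation, everyday stress and socioeconomic position to willingness to join the study (Target population and recruitment process). That these also drive attendance is an inference, though a reasonable one.

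**3. Size, by illustration.** The documents give no figure for this bias. All settings below are assumptions except the arm size, which is 45 × (1 − 0.21) = 35.55, taken as 36.
- Motivation U is standard normal, and the true booster effect is zero.
- Month-3 value: y3 = 0.4·e1 − (b/2)·U.
- Month-12 value: y12 = y3 + 0.45·e2 − b·U.
- Families allocated to boosters take part if U + e3 > 0, which is about half of them.
- e1, e2 and e3 are independent standard normal; 3,000 repetitions; two-sided 5% tests.

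| Confounding b | By allocation, adjusted for y3 | By participation | By participation, adjusted for y3 |
|---|---|---|---|
| 0 | 0.00; 5.0% | 0.00; 4.9% | 0.00; 4.2% |
| 0.15 | 0.00; 5.5% | −0.17; 15.3% | −0.11; 13.4% |
| 0.30 | 0.00; 5.2% | −0.34; 37.6% | −0.20; 27.7% |

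Each cell gives the mean estimate in BMI SDS and the false-positive rate.

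An analytical check of the third column: the mean of U among participants is √(1/π) = 0.564. Participants are a quarter of the sample, so the others average −0.564/3 = −0.188, a gap of 0.752. U enters y12 with total coefficient −1.5b. The expected bias is −1.5 × 0.15 × 0.752 = −0.17 and −1.5 × 0.30 × 0.752 = −0.34, matching the simulation. Adjusting for month 3 shrinks the bias but does not remove it.

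**4. What the contrast by allocation can deliver.** The plan states no power for it. Its figure of 75 per group concerns standard versus parent-group treatment and comes without an SD, so it cannot be reproduced. Solving for the SD with a difference of 0.3, two-sided 5%, 85% power and 75 evaluable per group gives 0.3 × √(75/2) / (1.960 + 1.036) = 0.613. With that SD and 35.55 per arm, the booster difference detectable with 85% power is 2.996 × 0.613 × √(2/35.55) = 0.44 BMI SDS, or 0.28 to 0.50 for assumed SDs of 0.4 to 0.7.

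**5. Month 3 as a covariate.** Boosters cover the last nine months, so month 3 falls at about their start. Let r0 and r3 be the correlations of 12-month BMI SDS with baseline and with month 3. The residual variance after adjusting for month 3, relative to adjusting for baseline only, is (1 − r3²)/(1 − r0²). The documents give neither correlation. Assume r0 of 0.75 to 0.85 and r3 of 0.85 to 0.92:
- r0 = r3 = 0.85 gives 0.2775/0.2775 = 1.00, a reduction of 0%.
- r0 = 0.75, r3 = 0.92 gives 0.1536/0.4375 = 0.35, a reduction of 65%.

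Adjusting for both values cannot leave more residual variance than month 3 alone. How much less depends on a third unknown correlation.

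**The case against.** The strongest reply is that Aim 2 should be read whole. It names the randomised conditions, and the hypothesis and the design section are both framed by condition. The parenthesis may only describe what separates the arms. Much of this stands: a reader might infer that the plan replaces the randomised comparison with one by attendance, but no passage says families will be regrouped or randomisation discarded. The reply fails for group attendance, which does not separate the arms at all. Nor can the point be left to an analysis plan, because the article states a definition rather than omitting one.

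Three further inferences are tempting and not supported.
- **That the month-3 measurement goes unused.** It is scheduled, and the growth model illustrated for Aim 1 spans the whole study. No Aim 2 model is shown, and a condensed article may leave that to a fuller document.
- **That adjusting for month 3 brings a definite, large gain in precision.** The assumed ranges allow anything from 0% to 65%, and the baseline-only comparator is not the plan's model.
- **That loss before month 3 cannot depend on booster allocation.** Ten weekly sessions can end before month 3, and the article does not fix the interval between baseline, group start and that visit. Some families may already know their allocation by then.

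**Conclusion.** The point holds as a mixed definition: one aim, two estimands, only one of them protected by randomisation. It does not show that the randomised analysis has been abandoned.

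If the literal definition were followed, the result would be open to confounding, probably in favour of families who engage more. The direction is not certain, since struggling families might take more calls. The 0.17 to 0.34 BMI SDS and the 15 to 38% false-positive rates depend entirely on the assumed confounding and vanish without it. They show the mechanism and do not estimate the trial's bias.

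The aim is secondary, but its conclusion is a headline claim about follow-up, so the wording should be settled before analysis. Use of month-3 BMI SDS is an optional refinement and no part of the defect.

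**What to change.** Reword Aim 2 so that the booster effect is allocated booster versus allocated no booster, with all families analysed as randomised and 12-month BMI SDS as the outcome. Name the model for this contrast.

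Label analyses by group attendance or number of boosters received as secondary and non-randomised. For booster participation, a complier-average effect with allocation as the instrument is an alternative. It does not serve group attendance, because the families do not learn their booster allocation until the groups are over.

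Optionally, if the month-3 visit is confirmed to precede both disclosure of allocation and the first booster, adjust this contrast for month-3 as well as baseline BMI SDS, or fit a separate slope from month 3.

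While Aim 2 is open, reconcile the booster interval: it says six weeks, while the section on parent group treatment gives four to six. The two describe the intensity being compared.

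The cost is a change of wording and one model specification. No new data, visits or families are needed.
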